**Figure 2 F2:**
[figure not shown]
Master data platform.

The experimental sample included 80 subjects aged 14 to 50 diagnosed with MDD (after administration of SCID-5 CV) who have been on stable medication for at least 16 weeks.

To achieve a 95% confidence level with a 5% margin of error in statistical sampling, considering a population proportion of approximately 50% and a known population size constituting 80% of the total, a minimum of 67 patients will be required. This calculation incorporates factors like the Z-score, standard deviation, and a finite population correction for larger populations. The meticulous consideration of these elements ensures the reliability and precision of the sample size, thus enhancing the credibility of the statistical findings in representing the broader population.

Participants will be excluded if they presented: intellectual disability; current or previously diagnosed psychotic disorder; mood disorder with psychotic features; bipolar disorder; alcohol and drug use with psychotropic effects according to DSM-5; pathologies of a chronic inflammatory nature; history of gastrointestinal disorders in the previous week; pregnancy.

The sample will be divided into two age groups (14–17 years and 18–49 years) and distributed in a randomized manner by random allocation in two different groups (group A and group B), each consisting of 40 subjects (10 adolescents and 30 adults).

Based on data from the Italian Statistical Institute (ISTAT) regarding the incidence of depression among italian adolescents, 20 teenager were included in the total sample.

Only the subjects assigned to group B will receive the technological equipment (Pothos system and smartwatch) for the collection of digital biomarkers; group A will be followed according to clinical standards of care. Specialized medical personnel will follow both groups from a pharmacological point of view.

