The assessment will include socio-demographic information, clinical history, medication details, and various clinical scales for evaluating depression severity (HAM-D, MADRS, CDI-2) and overall functioning (GAF, C-GAS, CBCL 6–18). Clinical parameters that will be monitored daily include: heart rate, and respiratory rate, oxygen saturation, light intensity, sleep/wake rhythm, and daily step count. The daily mood will be detected by using specific emoticons by the study participants. Additionally, vocal analysis will be conducted weekly using an “*ad hoc*” app to evaluate global articulation rate, fundamental frequency, and energy during specific tasks. Specific characteristics to be analyzed include F0 range (Hz), Energy per second (mV2), Average pause duration (s), Total pause time (s), and Variability of pauses (s).

The study will also include the collection of blood and saliva samples to assess inflammatory biomarkers (IL-1β, IL-2, IL-4, IL-5, IL-6, IL-10, IL-12, and IFNγ) and cortisol levels at the beginning (T0) and the end of the study (T1). Samples of peripheral blood and saliva will be taken in the group of patients with MDD and controls.

Blood withdrawal is necessary to recover the plasma and dose cytokines of pro- and anti-inflammatory cascade; the salivary sample allows the dosage of cortisol instead. Blood (7 ml) will be collected in K_2_-EDTA tubes, and plasma will be obtained through a density gradient centrifugation using SepMate™ Tubes. According to the manufacturer's instruction, blood will be diluted with PBS and then stratified on a gradient density medium (LymphoSep™, Biowest) that will allow the separation of plasma and other components after centrifugation at 1,200 × g for 10 min at a room temperature, brake on. Plasma will be recovered and stored at −80°C until it is used.

Saliva (>1 ml) will be collected in the morning, before brushing teeth and consuming food, through the use of a Salivette^®^ (Sarstedt), a test tube containing a swab to be chewed slowly for 2 min. Salivette^®^ will be centrifuged at 1,500 × g for 10 min at 4°C and then saliva will be recovered and stored at −20°C until the use.

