IL-1β, IL-2, IL-4, IL-5, IL-6, IL-10, IL-12, and IFNγ inflammatory biomarkers will be dosed in plasma through the Elisa test using ELISA Pro:Human Kits (Mabtech). IL-1α will be measured by using Interleukin-1α (human) ELISA kit (Cayman); cortisol will be quantified in saliva through a competitive assay (Cortisol ELISA Kit, Cayman). All the Elisa tests will be performed according to the manufacturer's instructions.

The study protocol and informed consent form were approved by the Campania Sud Review Board (application protocol: 48_r.p.s.o.).

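### The cytokine ELISAs are run on plasma recovered from blood already diluted with PBS, which lowers absolute concentrations by an unknown factor and may cost low values

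*Protocol article*

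**What the plan says.** The blood-handling text is in section 2 (Methods) of the protocol article, after Figure 2. The sequence is:

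- "Blood (7 ml) will be collected in" K2-EDTA tubes.
- "plasma will be obtained through a density gradient centrifugation using SepMate" tubes. This is the only route to plasma that the article gives.
- Before the spin, "blood will be diluted with PBS and then stratified on a gradient density medium"; centrifugation follows. The blood:PBS ratio is left to the manufacturer's instruction, which is not part of the document.
- "Plasma will be recovered and stored at" −80°C.
- The listed "inflammatory biomarkers will be dosed in plasma through the Elisa test", following the kit instructions.

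Sampling is at T0 and T1. The stated reason for drawing blood is to obtain plasma for cytokines; no assay on cells is named. Haematocrit is not among the listed assessments, and no expected concentrations or detection limits are given.

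**The concern.** After a gradient spin of diluted blood, the layer above the cells is not native plasma. It is the patient's plasma together with the PBS that was added. An ELISA on that layer reports a lower concentration than was in the patient. Following the kit instructions does not by itself correct this, because the dilution happened before the sample was frozen. The dilution also serves no purpose that the article names, since no cells are to be analysed.

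Two things are at stake. Absolute levels cannot be set against external values, or carried into a predictive tool, unless the true factor is known. And a concentration that falls below the assay limit because of dilution cannot be recovered by any later multiplication. Section 1.5 lists blood biomarkers among the predictors of recurrence or remission. Only group B receives the Pothos system and smartwatch, whereas nothing restricts blood sampling to one group, so this family of predictors should be available in both groups.

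**Working it through.** **Inputs.** From the article: 7 ml of blood; PBS added before separation; plasma recovered after it. The article states no dilution ratio, haematocrit or dilution factor, so there is no figure of its own to reproduce. Assumed: PBS:blood ratio r, with 1:1 (r = 1) as the working case and 0.25 to 3 as the range; haematocrit H from 0.38 to 0.50.

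**Formula.** One volume of blood holds 1 − H of plasma. Adding r of PBS gives a cell-free volume of (1 − H) + r. Plasma is therefore diluted by

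F = [(1 − H) + r] / (1 − H) = 1 + r/(1 − H).

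Example: 7 ml at H = 0.45 holds 7 × 0.55 = 3.85 ml of plasma. Adding 7 ml of PBS gives 10.85 ml, and F = 10.85/3.85 = 2.82.

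**Results.**

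| r (PBS per blood) | F at H = 0.38 | F at H = 0.50 |
|---|---|---|
| 0.25 | 1.40 | 1.50 |
| 0.5 | 1.81 | 2.00 |
| 1 | 2.61 | 3.00 |
| 2 | 4.23 | 5.00 |
| 3 | 5.84 | 7.00 |

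F exceeds 1 for every r above zero. Without the PBS step F = 1.

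**Would a nominal correction repair it?** At 1:1 the nominal blood dilution is 2. After multiplying by 2, values are still too low by F/2: 2.61/2 = 1.31 at H = 0.38 and 3.00/2 = 1.50 at H = 0.50. The PBS mixes with the plasma, not with the red-cell volume.

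**Effect on the assay limit.** An assay limit L in the recovered material corresponds to F × L in the patient's plasma, that is 2.6 L to 3.0 L at 1:1. How many values this would lose cannot be calculated without concentrations and limits.

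**Spread between patients.** At 1:1 the ratio of F at H = 0.50 to F at H = 0.38 is 3.00/2.61 = 1.15. For a typical spread, assume mean H = 0.42 and SD 0.04. Then the CV of F is about [1/(0.58²)]/2.72 × 0.04 = 0.044, or 4.4%. On the log scale the extra variance is 0.044² ≈ 0.0019. Against a biological variance of ln(1 + 0.3²) = 0.086 (CV 30%) this is about 2%; against ln(1 + 1²) = 0.693 (CV 100%) it is about 0.3%. These are also the proportional increases in sample size needed to offset it.

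**What cancels.** On the log scale, measured = true − log F. With r held constant, log F has the same expectation in both randomised groups. Within a patient, the T0 to T1 change is affected only if the haematocrit changes. Values lost below the limit do not cancel.

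**The case against.** The strongest reply has four parts.

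- **The size is assumed.** This stands. The ratio sits in an instruction that is not shown, and it matters far more than the haematocrit. A reader might take 2.6- to 3-fold as a property of the plan; it holds only at 1:1.
- **Loss below detection is not shown.** This also stands. A reader might infer that levels are already low because patients with "pathologies of a chronic inflammatory nature" are excluded. That exclusion says nothing about levels relative to an assay limit. Section 1.2 reports raised IL-6 and IL-12 in MDD, both on the assay list, while also mentioning low-grade inflammation in some patients. Loss of low values is a risk, not a result.
- **The comparisons of interest are largely protected.** This stands for a constant ratio. A reader might also infer serious confounding through haematocrit, which could vary with sex and age. At about 4% CV the effect is small, and adjusting for sex and age would take up much of it.
- **A journal article condenses the laboratory procedure.** The unstated ratio, any back-correction and the handling of non-detects may well be set out elsewhere, and their absence is no fault here. But the criticism rests on a step that is stated: the article says this is how the plasma is obtained. If an undiluted aliquot is in fact taken first, a sentence saying so closes the point.

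**Conclusion.** The point holds in a limited form. As written, the cytokine ELISAs use PBS-diluted plasma, so absolute concentrations are too low by 1 + r/(1 − H): about 2.6 to 3.0 at an assumed 1:1 and haematocrit 0.38 to 0.50, and about 1.4 to 7 for assumed ratios of 0.25 to 3. A nominal ×2 correction at 1:1 would leave values 1.3 to 1.5 times too low. Low values may be lost, to an extent the article does not allow anyone to calculate.

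The documents do not support a claim that the comparison of groups or of T0 with T1 is invalid, nor that haematocrit differences materially distort it. The case for change is that an avoidable loss of assay sensitivity and of interpretable absolute levels can be removed at almost no cost.

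**What to change.** Centrifuge the EDTA tube first and freeze undiluted plasma for all plasma ELISAs. Only then dilute the remaining cells with PBS for the gradient, if cells are wanted. If this is already done, state it.

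Process T0 and T1 identically for every patient. Switching a patient from diluted to undiluted plasma between visits would put the whole factor F into that patient's change, far more than the haematocrit noise it removes.

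Where T0 samples have already been diluted:

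- keep the same method and ratio for those patients at T1, and record the ratio;
- correct by 1 + r/(1 − H) only where a haematocrit is available, since the article does not list it as an assessment;
- analyse on the log scale, adjusting for sex and age;
- treat non-detects as left-censored.

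The cost is one short extra spin of the same 7 ml tube and a change of laboratory wording, with no extra blood or visit. The downside is the need to hold the processing method fixed within each patient.

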## 3 Results

The study's sample will first undergo initial age-based stratification. Subsequently, a more detailed categorization will be conducted based on outcomes observed during a 6-month follow-up period. This classification relies on remission, a crucial parameter indicating intervention effectiveness, determined by a HAM-D score ≤ 7. This stratification acknowledges age's impact on MDD manifestation and allows refined analysis of treatment outcomes in distinct age groups. Remission or clinical improvement presence will be confirmed using data from digital and environmental biomarkers, exploring connections between biomarkers, depression expression, disease course, and early illness signs.

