**Results:**

Following initial age-based stratification, the sample will undergo detailed classification at the 6-month follow-up based on remission status. Digital and environmental biomarker data will be analyzed to explore intricate relationships between these markers, depression symptoms, disease progression, and early signs of illness.

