## 1 Background

### 1.1 Epidemiology of Major Depressive Disorders

Close to one billion individuals globally grapple with mental health conditions, Major Depressive Disorders (MDD) is one of the most widespread among them (Institute of Health Metrics and Evaluation, 2022). MDDs are primarily distinguished by a reduction in energy and interest in daily activities, feelings of sadness, impaired concentration, sleep disturbances, emptiness, irritability, and the presence of suicidal ideation, planning, and attempts. With over 700,000 suicides reported annually, MDD stands as the fourth leading cause of death among individuals aged 15–29 years old (Malhi et al., 2018; World Health Organization, 2022). The onset of the disease occurs during adolescence in nearly 50% of cases, and a high risk of recurrence and chronicity across the lifespan in 5% of cases. Depression is about 50% more common among women than men (Lam et al., 2016).

After experiencing a first depressive episode, the recurrence rate within 3 years is more than 30%, and some patients have recurrent episodes; thus, the course of the disease can be chronic, placing a heavy burden on both patients and society (Kuehner, 2017). Despite its high prevalence, depression remains undiagnosed and untreated in half of all cases (Kohn et al., 2004).

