### 1.5 Aim of the study

This study focuses on evaluating specific digital and environmental biomarkers in adolescents and young adults diagnosed with MDD. The study, conducted through a prospective investigation on the MDD population (i.e., MDD), aims to:

Evaluate digital, environmental, and blood biomarkers as predictive indices of recurrence or remission of depressive pathology.Enhance digital technologies useful for predicting the severity of psychopathology and assessing treatment effectiveness.Apply technologies to distinguish individuals with depression and determine a personalized approach.Predict the severity of psychopathology among subjects using biomarkers derived from digital tools.

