## 2 Methods

This project, a prospective, randomized, interventional, and non-pharmacological integrated study (Figure 1), proposes a novel technological platform designed to collect, evaluate, and analyze a comprehensive range of digital and environmental biomarkers in adolescents and young adults diagnosed with MDD, through a prospective 24 months study. The platform adheres to principles of openness, integrability, and scalability to facilitate future advancements and its main components are described in Figure 2.

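### Classifying patients by HAM-D ≤ 7 at 6 months, without reference to their score at entry, counts sustained wellness as remission and gives recurrence no class of its own

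*Protocol article*

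**What the plan says.** The abstract (Results) states that "the sample will undergo detailed classification at the 6-month follow-up based on remission status". Section 3 repeats that "a more detailed categorization will be conducted based on outcomes observed during a 6-month follow-up period" and fixes the criterion: "This classification relies on remission, a crucial parameter indicating intervention effectiveness, determined by a HAM-D score ≤ 7". It then mentions remission or clinical improvement, but gives no criterion for improvement.

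The sample description in section 2 requires an MDD diagnosis by structured interview in patients "who have been on stable medication for at least 16 weeks". It lists exclusions in detail but states neither a minimum HAM-D nor a current episode.

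The first aim in section 1.5 is to "Evaluate digital, environmental, and blood biomarkers as predictive indices of recurrence or remission of depressive pathology". Section 4 restates it for relapse or remission. No criterion for recurrence or relapse appears anywhere in the article.

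Section 2 lists HAM-D among the assessments without a time point. The labels T0 and T1 are attached only to the blood and saliva samples.

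**The concern.** Three stated elements do not fit together: an outcome rule that looks at one score, an entry rule that allows a patient to be well already, and an aim that needs some patients to be well so that they can recur.

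For a patient at HAM-D ≤ 7 on entry, the same score at 6 months is an unchanged state. Calling it a sign that the intervention worked is wrong for that patient. In the other direction, a patient who was well and relapsed gets the same label as one who never improved, although these are opposite courses.

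The labels are the yardstick for the biomarkers and for the AI tool. If they largely reflect who was well at entry, a biomarker that tracks current severity will look like a predictor of remission while saying nothing about change. Recurrence, a named target, cannot be analysed because no class corresponds to it.

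**Working it through.** The article gives no expected number of remissions or recurrences, so there is no figure of its own to reproduce on this point.

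**Step 1. Cross the two visits.** Using the article's own cut at 7:

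| Entry HAM-D | 6-month HAM-D | Course | Label under the stated rule |
|---|---|---|---|
| > 7 | ≤ 7 | new remission | remission |
| ≤ 7 | ≤ 7 | sustained remission | remission |
| ≤ 7 | > 7 | relapse or recurrence | not remitted |
| > 7 | > 7 | persistent | not remitted |

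Four courses collapse into two labels, and each label mixes two different courses.

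**Step 2. Share of 6-month remissions already present at entry.** Let f be the share remitted at entry, s the share of those who stay remitted, and m the share of the others who newly remit. All three are assumptions, because the article gives none of them.

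Share = f·s / (f·s + (1 − f)·m), with s = 0.8–0.9 and m = 0.2–0.4.

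| f | Lowest (s = 0.8, m = 0.4) | Highest (s = 0.9, m = 0.2) |
|---|---|---|
| 10% | 0.08 / (0.08 + 0.36) = 18% | 0.09 / (0.09 + 0.18) = 33% |
| 20% | 0.16 / (0.16 + 0.32) = 33% | 0.18 / (0.18 + 0.16) = 53% |
| 30% | 0.24 / (0.24 + 0.28) = 46% | 0.27 / (0.27 + 0.14) = 66% |

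**Step 3. What a pure marker of entry state would show.** Under the same assumptions, a marker that only separates entry ≤ 7 from entry > 7 would meet 6-month remission rates of 80–90% against 20–40%. The odds ratio runs from (0.8/0.2)/(0.4/0.6) = 6 to (0.9/0.1)/(0.2/0.8) = 36, with no information about change.

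**Step 4. Is there enough recurrence to model?** Only the 40 patients in Group B have device data. With f = 10–30%, 4 to 12 of them are at risk.

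- Any crossing of 7, at 1 − s = 10–20%: 4 × 0.10 = 0.4 to 12 × 0.20 = 2.4 events.
- Section 1.1 puts recurrence at more than 30% within 3 years of a first episode. Taking 30% and a constant hazard, the 6-month risk is 1 − 0.70^(6/36) = 5.8%, which gives 4 × 0.058 = 0.2 to 12 × 0.058 = 0.7 events.
- Outer case, all 40 remitted at entry: 4 to 8 events on the first basis and 2.3 on the second.
- Followed for 24 months at the 30% rate, the risk is 1 − 0.70^(24/36) = 21.2%: 0.8 to 2.5 events with 4 to 12 at risk, and 8.5 with all 40.

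The two bases measure different things and should not be mixed. Every case listed is too small to train or validate a predictor of recurrence.

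**The case against.** The strongest reply is that the article is condensed. The full protocol may define recurrence, set a severity floor or condition remission on the entry score, and section 3's mention of clinical improvement suggests that change from an earlier state is intended. This has force: nothing says that entry HAM-D will be ignored, and the criteria permit remitted patients without showing that any are enrolled. What it does not answer is that the article states the parameter on which the classification relies, and that this parameter, followed as written, cannot separate the courses that the aims name. That is a problem with a stated rule and not only a missing detail.

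A reader might also infer stronger points that the documents do not support:

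- **A definite count of one or two recurrences.** The count depends on an assumed share at risk, on whether any crossing of 7 or a published recurrence rate is used, and on reading a lower bound as a rate.
- **Loss of power in the randomised comparison.** The article states no test of remission between Groups A and B, so there is no stated analysis against which to measure a loss.
- **A contradiction between 6 and 24 months.** Section 2 describes the work as carried out "through a prospective 24 months study". That may be the project's length with 6 months of follow-up per patient. The relation is unexplained but not contradictory.
- **That entry HAM-D is certainly recorded.** It is likely, but the article gives the scale no time point.

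**Conclusion.** The point holds as a defect in the stated classification rule. A single 6-month cut at HAM-D 7, in patients on stable medication with no stated severity floor, cannot tell new from sustained remission, merges relapse with non-remission, and leaves one of the two outcomes in the first aim without a definition.

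The direction of the error follows from the text alone. Its size does not. The 18–66% is an illustration on three assumed inputs, and the true share remitted at entry could be lower or higher than the 10–30% used. If nobody enters at 7 or below, the mislabelling disappears, but then nobody is at risk of recurrence at entry. A recurrence after a remission reached during follow-up would not be identified by one 6-month score either.

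**What to change.** 1. Classify by T0 and 6-month HAM-D together: new remission (T0 > 7, later ≤ 7), sustained remission (≤ 7 at both), relapse or recurrence (T0 ≤ 7, later > 7) and persistent (> 7 at both).
2. Count new remission only among patients above 7 at T0, and reserve any statement about effectiveness for that group.
3. Adjust biomarker prediction models for T0 HAM-D, so that a marker must add to what the entry score already tells.
4. Report the number at risk for each outcome, and treat recurrence prediction as descriptive, since few events are likely among 40 device users.
5. Confirm that HAM-D is recorded at T0, and state how T1 (the end of the study, for the samples) relates to the 6-month visit.

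If HAM-D is recorded at T0, this is a change of wording with no new data collection; if not, that assessment must be added. The price is that fewer patients contribute to the new-remission analysis: with 10–30% remitted at entry, 56 to 72 of the 80 (80 × 0.70 to 80 × 0.90).

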**Sensor integration:** The platform utilizes a core hub capable of integrating various sensors and smart devices (wearables, smartphones, “Pothos” air purifier) to collect physiological (e.g., heart rate, oxygen saturation), behavioral (e.g., activity, sleep, voice), and environmental data (e.g., CO_2_, fine dust, environmental brightness). The platform specifically uses Android-based smartwatches and smartphones because this software allows for easier integration with experimental programs like this one.**Mobile app:** An individualized mobile application will be developed by IT.Svil. s.r.l. with the purpose of enhancing patient engagement and simplifying communication with healthcare providers. This app will facilitate the collection of self-reported data from patients, thereby streamlining the healthcare process.**Data management:** To encourage collaboration among various components, a hub-and-spoke topology will be adopted. This approach ensures efficient interaction between different entities. The utilization of commercial cloud platforms is anticipated to optimize performance, cost-effectiveness, and security. Moreover, in line with privacy by design principles, the platform will prioritize data security through measures such as secure communication channels, VPN, MFA, and data encryption and anonymization techniques.**Deep learning analysis:** The platform utilizes advanced DL algorithms to analyze the collected data. These algorithms, based on neural networks, are adept at handling complex and diverse datasets. This is crucial because the platform will gather a wide range of information such as data types (e.g., digital, environmental, and biological) and data formats both discrete and continuous. By analyzing this data, the platform aims to uncover hidden patterns that can help to: improve diagnosis and tailor treatment plans to the individual's specific needs. The focus on DL underlines the platform's aim to become a modern and innovative decision support system that goes beyond simple data analysis.**Data standardization and applications:** Data will be structured according to international healthcare standards (e.g., International Patient Summary, IPS) for clear communication and analysis. Additionally, value-added applications for data visualization beyond basic time series dashboards are envisioned. IT.Svil. s.r.l.'s IT technicians, in collaboration with the research team, will undertake the development of the data visualization dashboard. This collaborative effort will ensure comprehensive input from various team members, resulting in an efficient and effective dashboard design.

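### The article describes no separation between the HAM-D remission rating and either allocation or device data, and has remission confirmed by the biomarkers that are meant to predict it

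*Protocol article*

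**What the plan says.** **Outcome.** Section 3 states that "a more detailed categorization will be conducted based on outcomes observed during a 6-month follow-up period", and then: "This classification relies on remission, a crucial parameter indicating intervention effectiveness, determined by a HAM-D score ≤ 7". This is the only outcome with a stated criterion. Section 2 also lists "various clinical scales for evaluating depression severity (HAM-D, MADRS, CDI-2) and overall functioning (GAF, C-GAS, CBCL 6–18"), and Section 1.5 names recurrence as well as remission, but none of these has a cut-off.

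**Predictors.** The first aim in Section 1.5 is to "Evaluate digital, environmental, and blood biomarkers as predictive indices of recurrence or remission of depressive pathology".

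**Link between the two.** Section 3 goes on: "Remission or clinical improvement presence will be confirmed using data from digital and environmental biomarkers".

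**Allocation.** Section 2 (Methods, after Figure 2) says: "Only the subjects assigned to group B will receive the technological equipment (Pothos system and smartwatch) for the collection of digital biomarkers". Group A has standard care, and no sham equipment is described.

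**Data flow.** Section 2 describes an app meant to ease contact between patients and those who care for them, and a platform that is to become a decision support system. IT technicians, "in collaboration with the research team, will undertake the development of the data visualization dashboard". On mood: "The daily mood will be detected by using specific emoticons by the study participants". That sentence is not limited to group B.

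The article does not say who scores the HAM-D, whether that person knows the group or the sensor data, or who may view the dashboard and when.

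**The concern.** A claim that biomarkers predict remission means something only if remission is established without them. Three features of the plan work against that.

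- The predictors cover the same ground as the illness being rated. Section 1.1 characterises depression by low energy, sadness and disturbed sleep. Section 2 records step count, mood and the sleep/wake rhythm.
- The platform is built to bring such data into clinical use, and anyone who meets a group B patient can see the equipment.
- Section 3 assigns the biomarkers a part in confirming remission.

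If the score, or the remission status derived from it, is influenced by the device data, agreement between marker and outcome is partly built in. Later analysis cannot remove it, because no uncontaminated score exists. Validating an AI tool is a declared goal of the study (Abstract and Section 4), so an inflated measure of prediction would affect its main product. The authors recognise rater subjectivity as a problem in Section 1.4, but describe no protection for their own reference outcome.

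Because remission is also described as a sign of intervention effectiveness, any comparison of remission between groups A and B would be exposed to the rater's knowledge of allocation.

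**Working it through.** **Figures in the plan.** The article gives no remission rate, no rater error and no expected AUC. Its one derived figure, a minimum of 67 patients, does reproduce: 1.96² × 0.25 / 0.05² = 384.15, and with a finite population of 80, 384.15 / (1 + 383.15/80) = 66.35, rounded up to 67. It concerns the precision of a single proportion and does not bear on this point.

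**The statements side by side.**

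1. Section 1.5: the biomarkers are predictors of remission.
2. Section 3: remission is HAM-D ≤ 7.
3. Section 3: remission or improvement is confirmed with the digital and environmental biomarkers.

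Statements 1 and 2 are compatible. Statement 3 makes the predictor part of establishing the outcome. This circularity stands in the text and needs no assumption about how a rater behaves.

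**Illustration of size (every input assumed).** Let p be true remission, 30–50%. Let a marker be positive in q = 50% of patients, independently of remission, so its true AUC is 0.50. Let a share s of discordant cases, 10–20%, end up classified in agreement with the marker, either when the score is given or when remission is confirmed. Then:

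- TP = pq + (1−p)qs
- FN = p(1−q)(1−s)
- FP = (1−p)q(1−s)
- TN = (1−p)(1−q) + p(1−q)s
- AUC of a binary marker = (sensitivity + specificity)/2

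For p = 0.3 and s = 0.2: TP = 0.15 + 0.07 = 0.22, FN = 0.12, FP = 0.28, TN = 0.35 + 0.03 = 0.38. Sensitivity is 0.22/0.34 = 0.647, specificity is 0.38/0.66 = 0.576, and AUC is 0.611.

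| p | AUC, s = 0 | AUC, s = 0.1 | AUC, s = 0.2 |
|---|---|---|---|
| 0.3 | 0.50 | 0.557 | 0.611 |
| 0.4 | 0.50 | 0.552 | 0.603 |
| 0.5 | 0.50 | 0.550 | 0.600 |

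**If groups A and B were compared on remission (again assumed).** Take 40 per group, equal true remission p of 30–50%, and a share s of 10–20% of group B non-remitters scored as remitters. The spurious difference is (1−p)s, from 0.5 × 0.10 = 5 percentage points to 0.7 × 0.20 = 14 points. With the normal approximation for two proportions, the chance of a two-sided p < 0.05 favouring group B is about 6.5% to 25%, against 2.5% in that direction without bias. The article describes no such test, so this is conditional. The direction is also an assumption: a rater who had seen poor sleep and low activity could score higher, which would reduce remission in group B.

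**The case against.** The strongest objection is that this is a condensed article and that an approved full protocol exists but is not shown. Rater identity, masking and dashboard permissions are details an article often leaves out. This stands as far as masking goes: silence is not evidence of open-label rating.

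Several stronger readings are tempting, and the documents do not support them.

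- *The HAM-D is scored open-label.* The article does not say so. A visible difference between groups shows that patients and treating staff know the allocation, but not that the rater does. That the scale is scored by an interviewer is itself an assumption here.
- *The rater sees the dashboard.* The text says only that the research team helps to develop it. It also mentions anonymisation.
- *Mood reports mark out group B.* The emoticon sentence refers to study participants generally.
- *HAM-D remission is the sole outcome.* Other scales are collected and recurrence is a target. It is the only one with a criterion.
- *The remission contrast between groups is biased.* No A-versus-B test, hypothesis or power is described; calling remission an indicator of intervention effectiveness only hints at one.

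The confirmation sentence might also be read as mere exploration of associations after remission is fixed, since it goes on to mention exploring connections. Its wording nevertheless gives the biomarkers a confirming role, and nothing in the article says that HAM-D takes precedence.

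**Conclusion.** The point holds in limited form. The article makes HAM-D ≤ 7 at 6 months both the prediction target and a marker of intervention effectiveness. It has the predictors confirm that outcome, in a design with visible allocation and a platform intended for clinical use. Followed as written, the plan does not secure an outcome independent of the predictors. The circular confirmation is documented. Contamination of the rating itself is a possibility that the article leaves open, not a fact that it states.

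The size is unknown. The AUC range of 0.55–0.61 for a worthless marker rests entirely on assumed remission of 30–50%, marker positivity of 50% and 10–20% of discordant cases moved. It shows that modest contamination would be enough to make a useless marker look weakly predictive. The between-group figures apply only if such a comparison is made. This is a cheap improvement worth making; it does not invalidate the study.

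**What to change.** 1. Have the HAM-D and MADRS at T0 and 6 months scored by a member of the existing team who does not treat that patient and has no access to the dashboard or app. The patient attends without the watch.
2. Lock the score before it is linked to that patient's device data.
3. Define remission by HAM-D ≤ 7 alone. Replace the sentence on biomarker confirmation with one saying that associations between biomarkers and the locked remission status will be examined.
4. Report that patients were unblinded to group, and state whether the raters were masked to group and to sensor data. If the full protocol already provides for masked rating, a sentence in the article saying so is enough for that part.

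Treating staff need not be kept from device data during follow-up: such a bar would conflict with the platform's monitoring purpose and is not needed if the rater is separate.

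The cost is some scheduling effort, an access rule on the dashboard and app, and occasional unmasking when a patient mentions the equipment. It assumes that the team has a non-treating member able to rate. No additional patients or visits are needed.
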